#### Interim and Subgroup Analyses

The interim analysis will be conducted after the initial pilot cohort have completed 4 weeks of the study.

### Sample Size and Statistical Methods

We aim to recruit 250 participants who have successfully completed the lead-in period and received the smartwatch to wear for the duration of their participation in the main study and lead-out periods. Assuming at least 75% of the participants complete the majority of the measures, a sample size of 250 will provide at least 80% power to detect correlations between passively collected data via the smartwatch and the actively collected data from ePRO instruments of at least 0.2 and over 90% power to detect correlations of at least 0.3 at any given time point. The analyses will not include any adjustment for multiplicity.

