## Abstract

**Background:**

Rheumatoid arthritis (RA) is a condition with symptoms that vary over time. The typical 3- to 6-month interval between physician visits may lead to patients failing to recall or underreporting symptoms experienced during the interim. Wearable digital technology enables the regular passive collection of patients’ biometric and activity data. If it is shown to be strongly related to data captured by patient-reported outcome (PRO) measures, information collected passively from wearable digital technology could serve as an objective proxy or be complementary to patients’ subjective experience of RA symptoms.

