### Analyses

#### Primary Analyses: Agreement Between ePRO and Passively Collected Digital Measures

The primary objective of this study is to quantify the agreement between passively collected digital measures (eg, activity) and ePRO data (eg, pain NRS scores). Descriptive statistics will summarize the demographics and baseline characteristics for all enrolled participants. The primary analysis will be a descriptive summary of the correlation between passively collected biosensor data and ePRO data. See Table 1 for a list of the ePRO and passively collected digital measures. For ePROs assessed weekly, multiple summary measures of the passive measures will be created over the corresponding weekly timeframe. Summaries to be explored include the average over the time period, trends, most recent, minimum, maximum, variation, and transformations in the data. Correlations between the ePRO and passive measures will be quantified using both a simple correlation matrix for each week as well as using repeated measures models over the entire study. Repeated measures models will be implemented using each ePRO as the outcome measure, with time (eg, week as a classification factor), baseline measures, and the various passive measures as potential factors in the model. The starting model will be a simple main effects model, and then a penalized regression model will also be used to optimize model selection, including the potential for 2-way interactions (including with time). This will allow for assessment of changes in correlations over time adjusted for participant level covariates.

For digital measures obtained daily, a repeated measures model will assess the association between the ePRO (outcome) and passive measures over time (with day as the time period of assessment rather than week). Daily ePRO data may lag by a day if it is observed that most participants are responding in the morning. Due to the large number of days in the study, time will be considered a numeric variable in this model.

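### The study is sized for one correlation at a time with no multiplicity adjustment, but each weekly matrix holds about 700 correlations, so the strongest pairs are overstated and hard to tell from chance up to about r = 0.27

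*Protocol article*

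**What the plan says.** Sample Size and Statistical Methods sets the size: "We aim to recruit 250 participants who have successfully completed the lead-in period and received the smartwatch". It continues: "Assuming at least 75% of the participants complete the majority of the measures", then "a sample size of 250 will provide at least 80% power to detect correlations" of at least 0.2, and "over 90% power to detect correlations of at least 0.3 at any given time point". The section ends: "The analyses will not include any adjustment for multiplicity".

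The section on primary analyses describes the main result as descriptive. For weekly ePROs it reduces each watch measure to several weekly summaries: "Summaries to be explored include the average over the time period, trends, most recent, minimum, maximum, variation, and transformations in the data". None is given priority. It then states: "Correlations between the ePRO and passive measures will be quantified using both a simple correlation matrix for each week", alongside repeated measures models and a penalized regression.

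The Introduction calls the study exploratory. The Abstract gives the purpose: "If it is shown to be strongly related to data captured by patient-reported outcome (PRO) measures", watch data might stand in for, or complement, what patients report. No value is given for what counts as a strong relation.

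**The concern.** The sizing and the analysis refer to different things. The power figures describe one correlation tested on its own. The primary analysis produces several hundred correlations per week, and readers will look first at the largest, because the question is which watch measures track the ePROs well. The largest of many estimates is biased upward even when every single estimate is unbiased, and this holds whether or not a p-value is attached.

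If noise alone commonly produces maxima within the range the study was sized to find, the article's best pairs cannot be separated from the best of several hundred chance results. A candidate proxy could be carried forward on that basis, and its strength would be overstated.

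**Working it through.** **Inputs from the protocol article.** Recruited: 250; evaluable: 75%, so 187.5 (188 used unless stated). Main study: 12 weeks. Weekly ePROs in Table 1: five PROMIS-CAT scales, OMERACT RA Flare and Godin, so 7. Watch measures in Table 1, by my count: 5 activity, 4 activity-derived, 1 heart rate, 1 heart-rate zone, 1 sleep and 5 sleep-derived, so about 17. Named summaries: 6, plus unspecified transformations.

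**Inputs assumed.** Alpha, sidedness and null value are not stated. I take two-sided 0.05 against r = 0. The correlations among watch measures, summaries and ePROs are also assumed, so ranges are shown.

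**Step 1: reproduce the stated power.** Fisher z: power = Φ(atanh(r) × √(n − 3) − 1.96), with √185 = 13.60.
- r = 0.2: 0.2027 × 13.60 = 2.757; Φ(0.797) = 78.7%. The noncentral t gives 79.5%.
- r = 0.3: 0.3095 × 13.60 = 4.210; Φ(2.250) = 98.8%.

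These sit close enough to the stated 80% and over 90% to support the assumed test. The small shortfall at 0.2 is within rounding of method and is not the point.

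**Step 2: count the correlations.** 7 × 17 × 6 = 714 per weekly matrix. With only 12 watch measures it is 7 × 12 × 6 = 504; with one transformation added, 7 × 17 × 7 = 833.

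**Step 3: what noise alone gives in one week.** The critical |r| at n = 188 is 1.973 / √(186 + 1.973²) = 0.143. Expected number beyond it: 714 × 0.05 = 35.7. The chance that a single null |r| reaches 0.2 is about 0.006, so about 714 × 0.006 = 4.3 are expected. Correlation among measures does not alter these expected counts, but it does alter the chance of at least one and the size of the maximum. These were therefore simulated with zero true association between ePROs and watch data.

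Simulation at n = 187, one weekly matrix:

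| Assumed correlation: ePROs / watch measures within domain / summaries | P(any p < 0.05) | P(largest \|r\| ≥ 0.2) | Median largest \|r\| |
|---|---|---|---|
| 0.5 / 0.5 / 0.3 | 100% | 91% | 0.23 |
| 0.6 / 0.7 / 0.6 | 100% | 77% | 0.22 |
| 0.7 / 0.9 / 0.8 | 96% | 46% | 0.19 |

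A separate simulation at n = 188 with somewhat different correlation structures gave a mean largest |r| of 0.23 (0.21 to 0.24), a 95th percentile of about 0.27 (about 0.26 to 0.28), and a probability of 83% (58% to 97%) that the largest reaches 0.2. The 46% and the median of 0.19 belong to the most strongly correlated setting only.

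**Step 4: does one summary per measure suffice?** That leaves 7 × 17 = 119 pairs. The chance of at least one p < 0.05 in a week under no association is still 88% (70% to 97%). Naming a lead summary helps, but a noise reference is still needed.

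**Step 5: what a strict correction would cost.** Bonferroni over 119 pairs: alpha = 0.05 / 119 = 0.00042, z = 3.527. Power at r = 0.2 is Φ(2.757 − 3.527) = 22%; at r = 0.3 it is Φ(4.210 − 3.527) = 75%.

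**The case against.** The strongest reply is that an exploratory, descriptive cohort need not control a familywise error rate, and that the authors disclose the lack of adjustment openly. That stands. The power sentence is also limited to a single time point, and it reproduces.

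A reader might infer that the plan contains a detection rule, r different from zero at 5%, that fires almost surely. The article states no such rule; it is only an inference from the power sentence. A reader might also infer that a chance correlation of 0.2 is certain every week. It is probable, not certain. The idea that chance findings would seem to replicate from week to week depends on an assumed week-to-week stability for every summary, including trend and variation, for which the article gives no figure. I do not rely on it.

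The Discussion itself cautions against chasing strong correlations, and few would call 0.27 strong, so a correlation well above 0.3 would clear the noise. The absence of any true association is a reference and not a forecast: the Introduction reports earlier associations. The penalized regression in the primary analysis shrinks model coefficients, but it does nothing for the weekly matrices. The cross-validation under Secondary Analyses serves the event and flare models.

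The full protocol or SAP may rank the summaries, and their silence here is no fault. What remains is what the article does fix: sizing for one pair, an open list of summaries, and a sentence excluding adjustment across all analyses.

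**Conclusion.** The point holds in a limited form. Declining formal adjustment is defensible, and the power statement is sound for one pre-specified pair. Without some reference for the maximum, however, the strongest pairs in each matrix will be overstated, and values from 0.2 up to about 0.26 to 0.28 cannot be told from the best of about 700 noise correlations. That covers most of the 0.2 to 0.3 range used for sizing.

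This rests on 188 evaluable participants, about 17 watch measures with all six named summaries entering each matrix, two-sided 0.05 against zero where significance is counted, and the assumed correlations among measures. Fewer measures or summaries, or stronger correlation among them, lower the noise maximum. It is a worthwhile, inexpensive improvement to reporting; it does not invalidate the study.

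**What to change.** In the section on primary analyses:
- Name the weekly average as the lead summary for each watch measure, and label the other summaries and the transformations hypothesis-generating.
- Keep reporting every raw correlation, with its confidence interval.
- Beside each matrix, show a permutation reference: re-pair whole watch records at random between participants, leaving each person's series intact, and give the 95th percentile of the largest |r|. False-discovery-rate q-values can be added as an option.

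In Sample Size and Statistical Methods:
- State that the power figures apply to a single pre-specified pair.
- Amend the multiplicity sentence to say that no formal correction is imposed and that the strongest correlations are read against the permutation reference.

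The cost is one extra analysis routine on data already collected, and more cautious wording for correlations below about 0.27. No further participants or procedures are needed. Mandatory Bonferroni correction is not recommended, because the loss of power in Step 5 would be out of proportion to a descriptive aim.

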## Results

A user flow was designed, developed, and tested for the lead-in and main study periods of the project. Screen shots displaying the user flow for the lead-in period are shown in Figure 3 and for the main study period in Figure 4. The study was launched in December 2018 with pilot participants. As of February 2019, 17 pilot participants have enrolled in the study, have completed the lead-in period, and have received a smartwatch and begun syncing their data as part of the main study period.

Invitations were sent to 70 eligible ArthritisPower participants, with a total of 17 participants enrolling in the pilot of the DIGITAL Study. Once they completed the lead-in period and successfully started the main study period, pilot participants provided feedback via email, online questionnaire, and phone calls. The research team also examined the ePRO and smartwatch data that had been collected from pilot participants to flag preliminary issues with participant adherence to protocol procedures and missing data. Three issues emerged that were addressed via modification to the operational plan and the app software (underlying user flow for this study).

First, participants appreciated getting daily reminders during the lead-in period and asked that these daily reminders continue throughout the main study period. Second, participants were confused about the difference between their ePRO measures for the week as part of the DIGITAL Study and the regular weekly ePRO measures completed within the standard ArthritisPower registry. This made it difficult for participants to distinguish whether they had completed their DIGITAL Study tasks for the day or week. As a result, we changed the ArthritisPower app user experience for those in the DIGITAL Study so that while ArthritisPower participants are taking part in the DIGITAL Study, their regular weekly ePROs in ArthritisPower will be disabled to avoid confusion and duplication of effort. Third, smartwatch data syncing presented some challenges for participants, with at least one participant in the pilot cohort believing they were syncing data correctly even though data were not appearing to the research team as expected. After troubleshooting, we discovered that the participant had logged in to a prior, personal Fitbit account, which meant data were not captured for analysis in the study during that period of their smartwatch use. Additionally, a few pilot participants said they found the smartwatch band to be uncomfortable and would take it off, sometimes forgetting to put it back on.

**Figure figure3:**
[figure not shown]
Lead-in period screen shots: a) Participant is presented with introductory screen, reminded of lead-in requirements to be eligible for the main study, and prompted to continue to assessments; b) Participant completes assessments, including daily single-item Fatigue measure; c) Upon completion of assessment queue, participant is reminded of remaining number of sets of assessments to be eligible for the main study.

**Figure 4 figure4:**
[figure not shown]
Main study period screen shots: a) Participant receives email and smartphone lock screen notification with reminder to complete daily and weekly assessments; b) Participant is informed of approximate time required to complete daily or weekly assessments so they can start when ready; c) Participant progresses through daily and weekly assessments, including Pain Interference; d) Upon completion of weekly assessment queue, participant sees a Health Picture summary of personal assessment scores.

We had planned several steps to minimize the technical trouble participants might encounter in syncing their smartwatch data and to enable the research team to quickly identify when smartwatch data was not being provided from a participant. First, in the Participant Kit that included the smartwatch, we provided simple set-up instructions on a “Start Here” 8.5”x11” card that included the Fitbit app download, and we included login information with a login email address and password that was unique to each participant. Since we knew in advance the participant’s login information, we could immediately see who was successfully syncing as soon as they set up their smartwatch. Second, in the ArthritisPower app unique user flow for the DIGITAL study, we prompted participants to let us know when they received their Participant Kit so they could be automatically directed to download the Fitbit app. This is scheduled to occur in the app after the lead-in period to inform the research team of the exact date a participant had taken the necessary steps to set up and sync their smartwatch. Finally, to minimize the risk of perpetual missing data from syncing or incomplete ePROs, we created a partially automated case management structure to rapidly identify participants whose data indicated the need for more intensive follow-up intervention, including calls from staff. To address watch band discomfort, the research team will now make alternative bands available to participants on a case-by-case basis when flagged during case management interactions. Importantly, we noted in the pilot cohort smartwatch data that if a participant removed their smartwatch, they did so either for a short period of time (eg, to shower) and put it back on fairly quickly, or for a long time (eg, to charge). As a result, for this study we agreed that at least one minute of activity or data in a given hour would indicate that the participant’s data could be used for analysis.

The DIGITAL study informed consent and study communications with participants were modified to reflect any changes to the initial operational plan following pilot cohort feedback. This exercise gave us greater confidence in participant data collected beyond the pilot cohort. It is expected that all study participants will have completed the main study period by early 2020 with results published in 2021.

## Discussion

The primary objective of this study is to evaluate the relationship between passively collected digital measures related to activity, heart rate, and sleep, collected from a smartwatch, with ePROs related to pain, fatigue, physical function, RA disease activity, and flare among people living with RA over 3 months. Since passively collected data, such as step counts and heart rate, are measured in a more continuous and objective manner than ePROs, there are implications for both research and patient care depending on the strength of the correlation between these two types of data.

For research, remote data collection of trial participants could minimize participant burden and save time and money required for clinical trials due to less frequent clinical visits and fewer staff hours. Among patients, both activity trackers and remote collection of ePROs mitigate recall bias and offer the opportunity for more comprehensive data collection. Our findings may help inform future studies by identifying when ePRO data are necessary to supplement passive data and when they are not. Collecting data during the interim period between clinician visits is important for patients with RA because each day can be different, so tracking variability in how the disease behaves day-to-day may help better assess disease activity. If ultimately accepted by regulators, this could lead to greater precision and thus smaller clinical trials, resulting in more rapid approval of medications for the marketplace. Moreover, this information facilitates a quicker and more continuous stream of real-world data being generated for comparative effectiveness research. As such, the type of approach represented in this protocol might be integrated into a complete, patient-centric digital health solution and bundled with a medication prescription, a so-called Beyond the Pill approach [21]. As a result, patients and clinicians may benefit from new information about therapies that are equally or more effective using data collected outside of a typical clinical setting. It could, for example, inform management of RA patients on combination therapy who are doing well (eg, in remission) and might consider discontinuing use of a drug without negatively affecting disease activity and symptoms.

Other possible benefits for patient care include the potential to identify treatment effectiveness between office visits, detect arthritis flare, accelerate clinical reevaluation, and speed up treatment modification when disease activity appears to be active, but this fluctuates frequently with intermittent flares. Monitoring patients remotely between visits in a manner that minimizes patient burden and does not require that a patient do more than wear a device could dramatically increase the amount and availability of data to inform specialists and primary care physicians about patients in their care, as well as contribute important information to assist with quality reporting and improvement [22].

There are several challenges related to passive data collection and the comparative analyses conducted with such data that we sought to address with this protocol. Wearables are appealing in terms of data collection over more hours each day, yet device selection is critical for patient adherence. Participants are more likely to be adherent for a longer duration when wearing commercial-grade devices that may lack the precision of fit for purpose research-grade devices. Passive data are available only when study participants remember to wear their device and correctly sync or download their data on a regular basis. To minimize the risk of missing data, we created a partially automated case management structure to rapidly identify participants requiring more intensive follow-up intervention. Passive data collection in the context of virtual studies such as this one requires more up-front investment of time to develop patient-centric onboarding materials and digital interfaces, operational plans for regular data review to identify issues with collection, and staffing to address questions that arise during technology onboarding and use.

Second, acceptable wear patterns must be established in advance to determine which downloaded device data actually indicate a participant’s use of the device for analytical purposes. The unit of measurement and associated time boundaries for analysis must be defined and described in the statistical analysis plans or programming requirements. For this study, we agreed that at least one minute of activity or data in a given hour would indicate that the participant’s data could be used for analysis. Comparison of continuous, minute-level data with data received only once daily or weekly makes the time cut-offs even more important and influential on results when lining up the data. Although tempting to seek strong correlations and good fitting models, there is substantial value in uncovering differences between passive real-time data and periodic ePRO measures. The increased variability and periodic divergence may lead to lower correlations, but they are also the reason multimodal assessment and an associated understanding of the different data streams is critical.

Finally, from a generalizability perspective, passive data collection requires participants that have a level of comfort with technology. The PARADE study observed that participants tended to have more years of formal education and be younger than the nationally representative cohort used for comparison [15]. Thus, research populations employing such technology represent a subsample that may not adequately represent important segments of patients with the disease in question.

The findings of this study may ultimately provide guidance for patient-focused drug development among regulators, specifically with the US Food and Drug Administration. A clearer characterization of how different types of patient-generated data describe the patient experience in a complementary fashion may help determine how and where to incorporate each data type into the regulatory decision-making process. Both ePRO measures and biometrics shed light on the patient experience, but on different aspects. Biometrics can continuously capture data like activity, heart rate, and sleep quality in a way that ePROs cannot, but there are aspects of activity, sleep, and other physical, mental, emotional, and social health domains related to biometric readings that biometrics alone are insufficient to understand. Daily and weekly ePRO measures like pain and fatigue that are being examined in this study are ideal for exploring the complementary nature of patient-reported and biometric data.

